### Power analysis

The power analysis is based on the primary outcome and endpoint, specifically the sum of eight items from WHODAS-12 at FU12. In the pilot trial (manuscript in preparation), a preliminary effect of 0.18 (Cohen’s *d*) was observed between the two care models after eight weeks of treatment. However, at that time, some of the GSH interventions were still ongoing. Many self-help books in the study are structured into 10–12 chapters, completed at a pace of one per week, and many of the studies on the internet-based interventions have a duration of 10–12 weeks [32, 34, 35, 37, 44]. Given this, the endpoint of this full-scale RCT was adjusted to twelve weeks, under the assumption that patients would have finished their treatments, which may produce a somewhat larger effect. A previous trial using similar GSH interventions reported slightly stronger effects [24]. Considering these factors, we estimate an expected between-group effect size of *d* = 0.20. To achieve 80% power with an alpha of 0.05 while accounting for 20% missing data at FU12, a total sample size of 983 patients is required [70]. Recruitment will continue until the power target is reached, with efforts to identify and include new PCCs as necessary. The pilot study (manuscript in preparation) demonstrated an acceptable inclusion rate.

If the primary analysis fails to establish superiority, a secondary analysis will assess whether the core PCBH model is non-inferior to the extended model (PCBH + GSH). No established non-inferiority margin exists for WHODAS-12 in mental health patients in primary care, and even less so for the 8-item version used in this study. Therefore, although not ideal, we reference a previously established non-clinically relevant difference of *d* = 0.24 from a meta-analysis of patients receiving psychological treatment for depression [71]. However, as this threshold is based on disorder-specific measures and treatments, we anticipate that the transdiagnostic WHODAS will be less sensitive to change and will therefore set the non-inferiority margin to *d* = 0.20. To achieve 80% power with an alpha of 0.05, assuming 20% missing data, 775 patients will be required [70]. This falls within the target sample size for the primary analysis. The smaller sample size required for the non-inferiority analysis, despite the identical effect size used, is due to the use of a one-sided test.

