In question (5), the difference in variation of treatment outcomes due to intervention (primarily comparing EXT-I-GSH with CORE-I-BI) will be evaluated by testing if the variation in FU12-scores differs between the two groups using an F-test. To put the difference in variation after treatment in context, the same type of F-test will be made on PRE-scores. The first question in (6) focuses solely on BI and how the therapists’ choice of methods affects outcome. This question requires rating all identified therapeutic methods based on the extent to which they are deemed to have an empirically supported effect for the condition they address. The protocol for these ratings will be developed once all therapeutic methods are identified and prior to exploring their relation to outcomes. The main analysis will be made on all patients receiving BI, regardless of subgroup. The second question in (6) examines potential differences between the subgroups receiving BI. For the third question in (6), only patients receiving GSH will be included, and ratings of therapist adherence will be used to explore its overall relationship to outcomes, as well as for subgroups of patients where GSH manuals with expected specific versus non-specific effects are used. For the final question in (6), relationships between treatment content and outcomes will be explored for all patients, regardless of care model or subgroup.

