For research questions (7), (8), and (9), the focus shifts to exploring the feasibility and fidelity of implementing the PCBH + GSH model at scale across multiple PCBH PCCs. To address research question (7), we will examine the proportion of patients who are deemed suitable for GSH following the extended diagnostic assessment. A hierarchical model using a binomial distribution will be used to evaluate whether the suitability rate varies significantly between as well as within centers over time, and to explore any factors contributing to these variations. In research question (8), we will use Hierarchical Linear Models to investigate how patient-related outcomes are affected by interventions and vary across centers and therapists, as well as the factors contributing to these differences. This will help identify potential barriers and facilitators for the successful implementation of both the core and extended PCBH models across different settings. Finally, research question (9) will explore the fidelity of both GSH and BI treatments. Specifically, we will examine how closely clinicians adhere to GSH principles within the PCBH framework, particularly in areas where GSH and PCBH principles may conflict, as well as generally assess the quality of the BI interventions. Fidelity scores will be analyzed descriptively to determine the frequency of low, good-enough and good fidelity ratings. A *t*-test will be used to evaluate whether the mean fidelity score is 3 (good-enough) or higher. Additionally, fidelity will be analyzed across clinicians and PCCs using chi-square tests and logistic regression to identify variability and the factors contributing to it. This will help assess the overall quality of treatment delivery and identify areas that may need further support or adjustment for large-scale implementation.

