The primary statistical methods employed will be Hierarchical Linear Models and Generalized Estimating Equations. Missing data will be handled using multiple imputation techniques that align with the missing data mechanism, while accounting for the multilevel structure of the data. Imputation models will be specified to reflect the underlying data structure, provided the complexity does not hinder model convergence. The analyses will consider the hierarchical structure of the data, such as nesting patients under therapists under PCCs for patient outcomes. The variance of each grouping level in the models will be calculated as the intra-class correlation (ICC) metric. An ICC > 0.10 will be used as a cutoff for the relevance of including it in the final model.

The non-inferiority analysis will be conducted by estimating the mean differences and standard errors at FU12, using Rubin’s rule after performing multiple imputations for missing data. A one-sided 95% CI (corresponding to a 90% two-sided CI) will be calculated for the estimated mean difference. To determine the outcome, we will compare the lower bound of the confidence interval with the non-inferiority margin of *d* = 0.20. If the lower bound of the CI is above this margin, non-inferiority will be established, in line with prior recommendations [72]. For research question (4), which hypothesizes that GSH protocols with assumed specific effects may demonstrate superior outcomes compared to BI, we will include a dummy variable in the model to represent the type of GSH protocol used (specific or non-specific).

For Health Economic Analyses in question (3), effectiveness will be assessed by constructing quality-adjusted life-years (QALYs) based on EQ-5D. Incremental cost-effectiveness ratios (ICERs) will be calculated, and Monte Carlo simulation with non-parametric bootstrapping will be conducted to address the uncertainty of the ICER point estimates. Cost-effectiveness acceptability curves (CEACs) will be employed to examine cost-effectiveness across varying willingness-to-pay scenarios.

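### The imputation plan lets cluster structure be dropped if it hinders convergence; if therapist and centre terms go, the ICCs and the research question 8 variances are biased downwards

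*Protocol article*

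**What the plan says.** The Data analysis plan section starts with a sound commitment: "Missing data will be handled using multiple imputation techniques that align with the missing data mechanism, while accounting for the multilevel structure of the data". The next sentence qualifies it: "Imputation models will be specified to reflect the underlying data structure, provided the complexity does not hinder model convergence". Convergence is the only stated criterion. The text does not say which part of the structure goes first, what replaces it, or whether any analysis is exempt.

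Three other statements in the section depend on the clustering.

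- The hierarchy is defined as "nesting patients under therapists under PCCs for patient outcomes".
- An ICC is to be computed for each grouping level, and "An ICC > 0.10 will be used as a cutoff for the relevance of including it in the final model".
- For research question 8, "we will use Hierarchical Linear Models to investigate how patient-related outcomes are affected by interventions and vary across centers and therapists".

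On the models, the plan says: "The primary statistical methods employed will be Hierarchical Linear Models and Generalized Estimating Equations". The non-inferiority analysis is expressly based on multiple imputation with Rubin's rule. Research question 5 is a different kind of analysis, namely "testing if the variation in FU12-scores differs between the two groups using an F-test", chiefly EXT-I-GSH against CORE-I-BI. The Power analysis section fixes the scale of the missing-data problem: the sample size was set while "accounting for 20% missing data at FU12".

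**The concern.** An imputation model that omits therapist and PCC draws each missing score around a common regression line. Imputed patients of a therapist with unusually good or poor results are pulled towards the overall mean, so the completed data show less clustering than there is.

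For most mean comparisons this is a side issue. Here the clustering is itself a target. Question 8 asks how far outcomes differ between centres and therapists, and the 0.10 rule uses the ICC to decide whether a level is relevant to the final model. One rule feeds the other: the convergence exception can lower the ICC, and the cutoff can then remove a level because of how the gaps were filled.

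**Working it through.** **Plan's own figures.** With d = 0.20, two-sided alpha 0.05 and 80% power, n per arm = 2(1.960 + 0.842)²/0.20², which gives 393 per arm and 786 in total; 786/0.80 rounds up to 983. For non-inferiority with one-sided 0.05, n per arm = 2(1.645 + 0.842)²/0.20², which gives 310 per arm and 620 in total; 620/0.80 = 775. Both match the Power analysis section. Neither is in dispute; the check takes N = 983 and m = 20% missing from it.

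**Assumed, not in the protocol.** 20 or 50 clusters; true ICC 0.12 or 0.15; total variance 1; correlation with FU12 of 0.5 for baseline and 0.7 for FU8; no cluster effect in the baseline score; FU12 values removed at random; five single-level regression imputations.

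**Formula, baseline only.** Observed patients (share 1 − m) carry the full cluster effect and imputed patients carry none. The cluster mean keeps a fraction 1 − m of the effect, so between-cluster variance is multiplied by (1 − m)² = 0.80² = 0.64.

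**Formula, FU8 observed for everyone.** FU8 passes on part of the effect.

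- Given baseline, Var(FU12) = 1 − 0.25 = 0.75.
- Given baseline, Var(FU8) = 0.49 × 0.75 + 0.51 = 0.8775.
- The covariance is 0.7 × 0.75 = 0.525, so the slope on FU8 is 0.525/0.8775 = 0.598.
- An imputed score carries 0.7 × 0.598 = 0.419 of the cluster effect.
- The factor is (0.80 + 0.20 × 0.419)² = 0.884² = 0.78.

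**Simulation, N = 983, 20% missing.**

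| True ICC | ICC, observed scores only | ICC, imputed from baseline only | ICC, imputed with FU8 for all |
|---|---|---|---|
| 0.12 | 0.117–0.119 | 0.075–0.077 | 0.092–0.093 |
| 0.15 | 0.145–0.149 | 0.093–0.094 | 0.114–0.118 |

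The simulated variance factors were 0.64 and 0.77 to 0.79, as the formulas predict. At 30% missing they were 0.48 to 0.50 and 0.68 to 0.70.

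**Effect on the 0.10 rule.** On average an estimate exceeds 0.10 only if the true ICC exceeds 0.10/0.64 = 0.156 (baseline only) or 0.10/0.78 = 0.128 (FU8 for all). True values between 0.10 and those limits would tend to be judged irrelevant.

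**Question 5, a separate mechanism.** Suppose the true variances are 1.5 and 1, and the 20% missing scores are imputed with one common residual variance. Imputed scores in both groups then have variance of about (1.5 + 1)/2 = 1.25. The completed-data ratio is (0.8 × 1.5 + 0.2 × 1.25)/(0.8 × 1 + 0.2 × 1.25) = 1.45/1.05 = 1.38. Simulation with an assumed 200 per group gave 1.37 to 1.38 without FU8 and 1.42 with it. A true ratio of 2.0 became 1.72 to 1.73 and 1.83 to 1.84. Adding treatment group as a predictor in the imputation model made no material difference (1.38 against 1.37).

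**The case against.** The strongest reply is that the order in which an imputation model is simplified is ordinary SAP detail, that the plan's first commitment is right, and that the exception may never be needed. Simplifying could mean dropping one level, a random slope or a complex time structure, with cluster information retained. Convergence also tends to fail when a variance component is near zero, and then little is lost. A separate SAP may settle the fallback. All of this limits the size of the point. It does not remove it, because the published text states a rule whose only test is convergence and exempts no analysis.

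A reader might infer more than the document supports, in four ways.

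- **That the plan does shrink these variances, or that the exception is likely to be used.** The protocol gives no therapist count, PCC count or cluster size, so the likelihood cannot be judged.
- **That the convergence clause causes the dilution in question 5.** It does not. The clause concerns the multilevel structure, and the dilution comes from a common residual variance, which the plan does not specify. Keeping therapist and PCC levels would not by itself cure it.
- **That imputation is unnecessary because a hierarchical model is planned.** This holds for the ICCs and question 8. It does not cover GEE, which under general missing-at-random needs imputation or weighting, nor the question 5 F-test, nor the non-inferiority analysis. Multiple imputation can also draw on the other repeated scales in Table 2, so it is a legitimate choice.
- **That the primary comparison is biased.** Randomization is individual, each PCC runs both models, and nothing here shows such an effect.

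**Conclusion.** The point holds as a conditional one. If convergence problems lead to removal of the therapist and PCC terms, the ICCs and the question 8 variance components are biased downwards. At 20% missing, between-cluster variance falls by about 22% to 36%. A true ICC of 0.12 then lies below the plan's cutoff throughout the range examined; a true 0.15 lies below it with baseline only, but above it if FU8 is available for everyone.

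These sizes rest on the assumed correlations, the assumed pattern of FU8 data and complete removal of cluster terms; a milder simplification would do less harm. The 0.10 decision changes only for true ICCs modestly above the cutoff, since 0.05 is below it either way. Questions 5 and 8 were added during the trial and are not primary. The change is still worth making before analysis, because a better method is available at almost no cost.

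**What to change.** 1. Estimate the ICCs, the variance components and question 8 by fitting the hierarchical model by (restricted) maximum likelihood to all observed PRE, FU4, FU8 and FU12 scores, without imputing the outcome. This is valid under missing-at-random given the data in the model. Table 2 schedules the 8-item WHODAS at all four points, and the Randomization and blinding section makes the pre-measure a condition of being analysed.
2. Keep multiple imputation for the non-inferiority and GEE analyses. Replace the convergence exception with a stated fallback that retains cluster information: PCC indicators, and therapist indicators where numbers allow. Indicators can slightly overstate between-cluster variance (0.12 became about 0.128 in a check with 40 therapists assumed), which is a further reason to take the ICCs from step 1.
3. Separately, for question 5: if imputed FU12 scores enter the F-test, impute by treatment group or with group-specific residual variances. Otherwise run the test on observed scores and state the missing-data assumption this needs. Imputing by group leaves fewer patients per therapist, so the fallback in step 2 should apply there too.

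The cost is a few sentences in the protocol or SAP. No new data or special software are needed.

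### Dropping a therapist or centre level whenever its estimated ICC is 0.10 or less can remove the level that research question 8 studies, and makes tests of therapist- and centre-level predictors anti-conservative

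*Protocol article*

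**What the plan says.** All of this is in the Data analysis plan section of the protocol article.

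- Methods: "The primary statistical methods employed will be Hierarchical Linear Models and Generalized Estimating Equations".
- The hierarchy is to be considered, "such as nesting patients under therapists under PCCs for patient outcomes".
- Each level is then judged separately: "The variance of each grouping level in the models will be calculated as the intra-class correlation (ICC) metric". The next sentence sets the rule: "An ICC > 0.10 will be used as a cutoff for the relevance of including it in the final model".
- Research question 8 is assigned to Hierarchical Linear Models, to investigate "how patient-related outcomes are affected by interventions and vary across centers and therapists" and what contributes to the differences.

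The rule follows a general statement about the analyses and carries no exemption for any research question. The section does not say at which level Generalized Estimating Equations (GEE) would cluster.

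**The concern.** Two things go wrong if the rule is followed as written.

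First, it conflicts with research question 8. To ask how outcomes "vary across centers and therapists, as well as the factors contributing to these differences", the model must contain the centre and therapist levels. The rule removes either one when its estimated ICC is 0.10 or less.

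Second, the ICC alone is the wrong criterion. For a predictor that is constant within a cluster, such as a therapist or centre characteristic, the variance of its estimated effect is multiplied by a factor that grows with both the ICC and the number of patients per cluster. With the level gone and no clustered standard errors, the test treats patients of the same therapist as independent and rejects too often. At stake is a false claim that some therapist or centre factor explains differences in outcome.

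**Working it through.** **Planned sample size, reproduced.** Inputs from Power analysis: d = 0.20, 80% power, alpha 0.05 (taken as two-sided), 20% missing.
- Superiority: 2 × (1.960 + 0.842)² / 0.20² = 392.4, so 393 per arm and 786 in total; 786 / 0.8 = 982.5, rounded up to 983, as stated.
- Non-inferiority, one-sided 0.05: 2 × (1.645 + 0.842)² / 0.20² = 309.1, so 310 per arm and 620 in total; 620 / 0.8 = 775, as stated.

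Neither figure contains a clustering term, nor any gain from modelling therapist or centre.

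**Predictors that vary only between clusters.** The protocol gives no number of therapists or PCCs, no patients per therapist and no expected ICC, so cluster size m and the true ICC are assumptions here. If the level is always dropped:

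DEFF = 1 + (m − 1) × ICC; actual two-sided error = 2 × [1 − Φ(1.96 / √DEFF)].

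Example with m = 20 and ICC = 0.05: DEFF = 1 + 19 × 0.05 = 1.95; 1.96 / √1.95 = 1.404; error 16.0%.

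The plan's rule is not always-drop. It drops the level only when the estimated ICC is 0.10 or less. This two-step rule was simulated: 4,000 runs per scenario, 800 patients, equal clusters, and a cluster-mean test when the level is kept. Monte Carlo standard error at 15.5% is √(0.155 × 0.845 / 4000), about 0.6 points.

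| Patients per cluster (clusters) | True ICC | DEFF | Error if always dropped | Error under the full rule | Trials in which level is dropped |
|---|---|---|---|---|---|
| 10 (80) | 0.01 | 1.09 | 6.0% | 5.7% | 100% |
| 10 (80) | 0.05 | 1.45 | 10.4% | 9.3% | 98% |
| 10 (80) | 0.10 | 1.90 | 15.5% | 8.9% | 52% |
| 20 (40) | 0.01 | 1.19 | 7.2% | 7.5% | 100% |
| 20 (40) | 0.05 | 1.95 | 16.0% | 15.5% | 99% |
| 20 (40) | 0.10 | 2.90 | 25.0% | 13.8% | 54% |
| 50 (16) | 0.01 | 1.49 | 10.8% | 10.5% | 100% |
| 50 (16) | 0.05 | 3.45 | 29.1% | 27.4% | 97% |
| 50 (16) | 0.10 | 5.90 | 42.0% | 22.8% | 55% |

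At a true ICC of 0.05 the level is almost always removed, and the full rule behaves like always-drop. At 0.10 it survives in nearly half of trials, so the always-drop formula overstates the error.

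**Predictors that vary within therapist.** If the predictor itself has intra-therapist correlation r (assumed), DEFF = 1 + (m − 1) × ICC × r. With m = 20 and ICC = 0.05:
- r = 0.3: DEFF = 1 + 19 × 0.05 × 0.3 = 1.285; error 8.4%.
- r = 0.1: DEFF = 1.095; error 6.1%.
- r = 1 (constant within therapist): 16.0%, as in the table.

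**The randomised comparison.** Allocation is individual (Design and overall procedure) and each PCC runs both arms (Discussion). Dropping a level leaves its variance in the error term, so the standard error is larger by 1 / √(1 − ICC):
- ICC 0.05: factor 1.026; power with 786 analysed is 82.0% if the level is kept, against 80.1% if dropped.
- ICC 0.10: factor 1.054; 84.0% against 80.1%.

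Simulated type I error with the level dropped was 4.2-5.7% across scenarios, which shows no inflation. These figures assume no therapist-by-arm variation.

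**The case against.** **The specific plan governs its own question.** Research question 8 is expressly given to hierarchical models, and each level's ICC is computed in any case, which already describes the variation. This is a fair reading, but the text does not say it. The cutoff is stated for the final model without exception. An ICC also only describes variation; the factors that contribute to it still have to be tested in a model with correct standard errors.

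**GEE is also named.** Robust standard errors clustered on therapist or PCC would avoid much of the problem, and an article may leave the clustering unit to the analysis plan. That is true in general, but research question 8 is assigned to Hierarchical Linear Models, so naming GEE does not resolve it.

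**The affected questions are secondary.** Research questions 5-9 were added during the trial (Preregistrations and current protocol), and questions 6-9 are largely exploratory. This lowers the stakes; it does not make the rule sound.

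Some stronger readings are tempting, and the documents do not support them:
- *A fixed false-positive rate, such as 10-30%.* No such figure follows from the protocol, because it gives neither cluster sizes nor ICCs. With small clusters and an ICC near 0.01 the error stays close to nominal.
- *The same inflation for treatment methods and adherence (question 6) or for guided self-help against brief interventions.* Treatment content is extracted from medical records and fidelity is also scored per treatment (Treatment content; Fidelity to GSH protocols and BI principles). All clinicians are trained in guided self-help (Training and supervision). These predictors can therefore vary within therapist, and inflation is much smaller.
- *A threat to the primary comparison.* The effect there is conservative and small.
- *The fidelity t-test under research question 9.* It lies outside the ICC rule and is a separate point, not claimed here.

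**Conclusion.** The point holds in a limited form. The protocol states a rule that, taken literally, can delete the level that research question 8 needs, and that leaves tests of purely therapist- or centre-level predictors anti-conservative unless standard errors are clustered. At a true ICC of 0.05, actual error at nominal 5% runs from about 10% to about 27% as clusters grow from 10 to 50 patients; at ICC 0.01 with 10 patients per cluster it is only about 5-6%. These sizes rest on assumed, equal cluster sizes and assumed ICCs, and on model-based standard errors once the level is dropped.

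For the randomised comparison there is no loss of validity. The standard error is at most about 5% larger per dropped level, and the planned 80% power stands because 983 never counted on that gain. The change is worth making for the therapist- and centre-level questions, not to rescue the primary result.

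**What to change.** Remove the ICC > 0.10 cutoff. State that therapist and PCC are kept in the patient-outcome models whatever their estimated ICC; at the very least, state this for research question 8 and for any predictor measured at therapist or centre level. Report the ICCs descriptively. Simplify a model only if it fails to converge, and then use cluster-robust standard errors. The section already uses convergence as the limit on complexity for its imputation models, so this would bring the analysis models into line with them.

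The cost is a change of wording, since the models are already hierarchical and the protocol was written before analyses start. The downside is occasional zero-variance estimates or convergence problems, and wider intervals for the therapist- and centre-level questions. The sample size does not change.

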**Methods:**

Patients seeking help for mental or behavioral health problems at PCBH primary care centers will be randomized to one of two arms: core PCBH, where patients receive a contextual assessment and brief interventions tailored to their needs, or an extended PCBH model, where a diagnostic assessment determines whether patients receive brief interventions or guided self-help. The primary outcome is functional impairment, assessed at baseline and followed up at 4, 8, and 12 weeks (primary endpoint), as well as at 1 year. Secondary outcomes include symptom change, cost-effectiveness, and care process factors.

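### The printed non-inferiority rule (lower confidence limit above d = 0.20) is not a non-inferiority test under either coding of the difference, and would almost never declare core PCBH non-inferior when the arms are equal

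*Protocol article*

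**What the plan says.** The Power analysis section makes non-inferiority of core PCBH to the extended model a secondary analysis, run if superiority is not shown. The first research question under Aim and purpose has the same order. The authors "set the non-inferiority margin to *d* = 0.20", a positive number with no direction. The sample size follows: "To achieve 80% power with an alpha of 0.05, assuming 20% missing data, 775 patients will be required". It is smaller than the superiority sample size of 983, and the section gives the reason: "The smaller sample size required for the non-inferiority analysis, despite the identical effect size used, is due to the use of a one-sided test".

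The Data analysis plan sets the decision rule. "A one-sided 95% CI (corresponding to a 90% two-sided CI) will be calculated for the estimated mean difference". Then "we will compare the lower bound of the confidence interval with the non-inferiority margin of *d* = 0.20", and finally "If the lower bound of the CI is above this margin, non-inferiority will be established".

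On the outcome, the Methods paragraph of the Abstract says "The primary outcome is functional impairment". The Measures section labels the same eight WHODAS items everyday functioning. The article does not say whether a higher score is better or worse, nor which arm is subtracted from which.

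**The concern.** A non-inferiority claim needs the confidence limit on the unfavourable side to stay inside the margin. The printed rule asks for a limit that lies beyond +0.20, so the whole interval must sit outside the margin on the positive side.

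This rule settles the fallback conclusion of the primary research question, and non-inferiority of BI is also asked for the subgroups in question 2. The article says that it exists to specify methods before analyses start, so the rule is fixed in this document and not left open. If it is corrected only after results are known, the correction will look like a change of criterion made to suit the data.

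**Working it through.** **Inputs (protocol article).** Margin d = 0.20; one-sided alpha 0.05 for non-inferiority; 80% power; 20% missing at FU12; totals of 775 (non-inferiority) and 983 (superiority); 1:1 allocation. Normal approximation, SD = 1, clustering ignored.

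**1. Reproduce the article's sample sizes.**
- Non-inferiority, true difference 0, one-sided 5%: n per arm = 2 × (1.645 + 0.842)² / 0.20² = 309.1, rounded up to 310. Total 620; 620 / 0.8 = 775. Exact match.
- Superiority, two-sided 5%: n per arm = 2 × (1.960 + 0.842)² / 0.20² = 392.4, rounded up to 393. Total 786; 786 / 0.8 = 982.5, rounded up to 983. Exact match.

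The 775 therefore rests on the conventional rule: the limit on the unfavourable side stays within 0.20, with 80% probability when the arms are equal.

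**2. Read the printed rule under each coding.**
- Core minus extended, higher = worse: a lower limit above +0.20 shows that core is worse by more than the margin.
- Positive = core better: a lower limit above +0.20 shows that core is better by more than 0.20.

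Neither is non-inferiority.

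**3. Estimate that the printed rule requires.** SE = √(2 / n analysed per arm); required estimate = 0.20 + 1.645 × SE.

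| Total N | Analysed per arm | SE | Required estimate |
|---|---|---|---|
| 775 | 310 | 0.0803 | 0.332 |
| 983 | 393.2 | 0.0713 | 0.317 |

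**4. Probability of declaring non-inferiority when the arms are equal.** Printed rule: 1 − Φ(required estimate / SE). Conventional rule: Φ(0.20 / SE − 1.645).

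| Total N | Printed rule | Conventional rule |
|---|---|---|
| 775 | 0.000018 | 80.1% |
| 983 | 0.000004 | 87.7% |

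Under the conventional rule, the chance of a claim when core is truly worse by exactly 0.20 is 5.0% at either N.

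**5. Effect of testing superiority first.** With core minus extended at N = 983, PCBH + GSH is shown superior once the estimate exceeds 1.96 × 0.0713 = 0.140. The printed non-inferiority rule needs more than 0.317. Any result that meets it has already established superiority, so the non-inferiority step is not reached. With a common SE this holds whenever 0.20 + 1.645 × SE > 1.96 × SE, that is SE < 0.20 / 0.315, about 0.63. Since SE = √(2 / n), this is more than about 5 analysed patients per arm (2 / 0.63² = 5.0), so it covers any realistic subgroup.

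**The case against.** The strongest reply is that this is a missing sign in a condensed article. The Power analysis gives the margin as a magnitude, and the 775 shows that a conventional test was intended. If positive values favour core, the lower limit is the right one and only a minus sign is absent. That is probably what was meant. It does not remove the point, because the printed sentence gives no sign and no direction, and a reader cannot apply it as it stands.

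Four stronger readings are tempting, and the document does not support them.

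- **A false claim when core is clearly worse.** In isolation, with core minus extended and core truly 0.40 SD worse, the printed rule would be met 88% of the time at N = 983 (80% at N = 775). But the test runs only if superiority fails, and step 5 shows that every such result has already shown PCBH + GSH superior. With the opposite coding, the rule is met only by results favouring core. The false claim does not arise in the planned sequence.
- **Both the limit and the sign are wrong.** The direction is undefined, so one correction is enough. Switching to the upper limit and also making the margin negative would again give a wrong rule.
- **The one-sided 5% level is an error.** It is stated openly, explained, and consistent between the Power analysis and the Data analysis plan. A stricter level would be a preference.
- **The standardising SD is missing.** The interval is for a mean difference and the margin is in d, so the two need common units, but which SD to use is detail that an analysis plan may hold.

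**Conclusion.** The rule is wrong as printed: no coding of the difference makes it a non-inferiority test, and it contradicts the article's own sample size calculation. In the planned sequence the consequence runs in the conservative direction. With equal arms, non-inferiority would be declared with probability about 0.000004 instead of about 88% at N = 983 (0.000018 instead of 80% at N = 775), so the fallback conclusion is in effect unavailable.

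These figures rest on a normal approximation, 20% missing data, equal arms after loss and no clustering. Clustering would change the exact probabilities but not the finding. Higher = worse is inferred from the impairment label, since the article does not state it; under the opposite coding the printed rule fails equally. The step 5 argument takes the superiority test as two-sided 5%, as the 983 implies; a one-sided 5% test would have a lower threshold still (1.645 × 0.0713 = 0.117), and the argument would hold all the more.

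**What to change.** State the direction of scoring and of subtraction, then use one of two equivalent rules:

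- difference = core PCBH minus PCBH + GSH in WHODAS-8 at FU12, higher = worse: core PCBH is non-inferior if the upper limit of the one-sided 95% confidence interval is below +0.20 SD; or
- difference coded so that positive values favour core PCBH: core PCBH is non-inferior if the lower limit of the one-sided 95% confidence interval is above -0.20 SD.

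Express the interval and the margin in the same units, either both standardised or both in WHODAS points. Apply the same signed rule to the question 2 subgroups, with BI in place of core PCBH.

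The cost is a few sentences. The one-sided 5% level, the 775 and the 983 stay as they are, and no extra patients are needed. Make and date the correction before outcome data are analysed, and list it in the deviations section that the article already promises for trial reports.
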